## Abstract

**Background:**

Type 2 diabetes (T2D) brings significant human and healthcare costs. Its progressive nature means achieving normoglycaemia is increasingly difficult, yet critical to avoiding long term vascular complications. Nearly one-half of people with T2D have glycaemic levels out of target. Insulin is effective in achieving glycaemic targets, yet initiation of insulin is often delayed, particularly in primary care. Given limited access to specialist resources and the size of the diabetes epidemic, primary care is where insulin initiation must become part of routine practice. This would also support integrated holistic care for people with diabetes. Our Stepping Up Program is based on a general practitioner (GP) and practice nurse (PN) model of care supported appropriately by endocrinologists and credentialed diabetes educator-registered nurses. Pilot work suggests the model facilitates integration of the technical work of insulin initiation within ongoing generalist care.

**Methods:**

This protocol is for a cluster randomized controlled trial to examine the effectiveness of the Stepping Up Program to enhance the role of the GP-PN team in initiating insulin and improving glycaemic outcomes for people with T2D. 224 patients between the ages of 18 and 80 years with T2D, on two or more oral hypoglycaemic agents and with an HbA1c ≥7.5% in the last six months will be recruited from 74 general practices. The unit of randomization is the practice.

Primary outcome is change in glycated haemoglobin HbA1c (measured as a continuous variable). We hypothesize that the intervention arm will achieve an absolute HbA1c mean difference of 0.5% lower than control group at 12 months follow up. Secondary outcomes include the number of participants who successfully transfer to insulin and the proportion who achieve HbA1c measurement of <7.0%. We will also collect data on patient psychosocial outcomes and healthcare utilization and costs.

**Discussion:**

The study is a pragmatic translational study with important potential implications for people with T2D, healthcare professionals and funders of healthcare though making better use of scarce healthcare resources, improving timely access to therapy that can improve disease outcomes.

**Trial registration:**

Australian and New Zealand Clinical Trials Registry ACTRN12612001028897

## Background

Type 2 diabetes (T2D) is a costly, epidemic condition [1,2]. In Australia, T2D is anticipated to be the leading cause of disease burden by 2016 [2], costing over $14 billion annually in direct and indirect healthcare costs [3], and shortening life expectancy by up to five years. We can expect an exponential rise in the human and healthcare costs associated with T2D [4].

Because T2D is a progressive condition, involving beta cell failure in the presence of insulin resistance, normoglycaemia is increasingly difficult to achieve [5]. Hyperglycaemia causes microvascular and macrovascular complications through glycation and oxidation of proteins [6]. Conversely, achieving optimal glycaemic control early in the course of the disease reduces the risk of vascular complications as well as mortality [7]. The most recent Australian Diabetes Society (ADS) guidelines [8] recommend individualized glycaemic targets (HbA1c) based upon diabetes duration, age, and co-morbidity, yet in Australia, only 52% of people with T2D achieve an HbA1c below 7% (53 mmol/mol).

Early use of insulin as a part of treatment intensification for people with T2D is supported by both American and European guidelines [9-11]. The effectiveness of insulin in improving glycaemic control in T2D has been shown in clinical trials, largely in secondary care [12-15]. The use of long-acting insulin analogues with simple patient-driven algorithms is feasible, safe (low incidence of hypoglycaemia), effective in achieving glycaemic control [13,14], and associated with improved patient satisfaction [16].

Despite evidence of the effectiveness of insulin and endorsement of its early use in guidelines, in practice, initiation of insulin is often delayed. The mean HbA1c of people with T2D prior to starting insulin is 9.4% (79.2 mmol/mol) in Australia (after a median diabetes duration of 8.1 years) [17], and 9.3% (78.1mmol/mol) in the UK [18], well above recommended targets. This has been attributed, in part, to ‘psychological insulin resistance’ (negative perceptions and attitudes that act as barriers to starting insulin) [19] among people with T2D and ‘clinical inertia’ (recognition of a problem but failure to act) among practitioners [20]. However, health system factors also play a role. While the majority of care for people with T2D takes place in general practice, insulin initiation is commonly deferred to specialist diabetes service [21,22], and the majority of Australians with T2D initiate insulin within specialist settings [23]. Difficulties accessing endocrinologists and diabetes nurse educators because of cost and limited availability can lead to delays in starting insulin, and avoidable periods of hyperglycaemia.

While specialist diabetes services have a role in managing complex cases, initiating insulin in routine general practice has several benefits. For example, diabetes care can remain integrated with care for other conditions, as glycaemic control is often just one facet of managing multiple co-morbidities. Furthermore, as secondary care is costly [24], there are considerable economic benefits to retaining T2D care in general practice. However, achieving timely and effective insulin initiation as a routine aspect of care in general practice presents some challenges. GPs are more reluctant than specialists to start insulin [25], and up-titrating to achieve glycaemic targets is also a challenge. A Canadian trial utilising community pharmacists and specialist nurses to support general practice-based insulin initiation did not show any improvement in insulin prescribing rates or in glycaemia [26]. An intensive educational intervention for GPs and PNs in the UK has been evaluated using clinical audit data from 115 practices; it showed significantly improved glycaemic control at six months in patients who started insulin, although further improvement was not observed over 36 months [27]. In Australia, 63% of general practices employ close to eleven thousand PNs across the country [28]. They are a rapidly growing sector of the primary care workforce and now core members of the general practice team supported by significant government investment.

We have designed and piloted for feasibility [29] an education and system-change intervention (the Stepping Up Program—described in more detail below) to facilitate general practice-based insulin initiation in people with T2D and suboptimal glycaemic outcomes who are on maximum oral therapy. The program is based on a model of care that focuses on the ‘in-practice team’ (GP and PN), supported appropriately by endocrinologists and credentialed diabetes educator-registered nurses (CDE-RNs). Our model acknowledges the importance of endocrinologists and CDE-RNs in providing support to GP/PN teams in initiating insulin when needed. Our pilot work [29] highlighted how this model of care supported integration of the technical work of insulin initiation within ongoing generalist care. Issues of clinical accountability and flexibility, managing time and resources were highlighted as important.

In this paper, we describe the protocol for a cluster randomized controlled trial to examine the effectiveness of the Stepping Up Program to enhance the role of the GP-PN team in initiating insulin and improving glycaemic outcomes for people with T2D. Our primary outcome is change in HbA1c (measured as a continuous variable). We hypothesize that participants in the intervention arm will achieve an absolute HbA1c mean difference of 0.5% lower than control group participants at 12 months follow up. Secondary outcomes are described below.

## Methods

This study is a cluster randomized controlled trial, conducted in 74 general practices across the Australian state of Victoria. The consort diagram is provided in Additional file 1. Ethical approval was received from the University of Melbourne Health Sciences Human Research Ethics Sub-committee (ID 123740). The trial is registered with the Australian and New Zealand Clinical Trials Registry (ACTRN12612001028897).

### Recruitment and randomization of practices

Eligible general practices must have a current PN. Practices are recruited using our University Department of General Practice database (the VicREN practice based Research Network) and through Medicare Locals. Practice randomization is stratified by practice size, location in Community Health Centers, and participation in the National Primary Care Collaboratives.

The unit of randomization is the practice. Practices are randomized after consenting, and following recruitment of at least one eligible patient (Additional file 1). Due to the nature of the intervention and because further patient recruitment often occurs over a period of months subsequent to randomization, full allocation concealment is not possible. Randomization is in blocks, undertaken by a statistician at the University of Melbourne independent of the research team. Following randomization, the research team assist practices to continue to identify and recruit patients.

### Participant eligibility

Eligible patients are those with most recent HbA1c (in the previous six months) ≥7.5% and who are on maximal oral therapy but not currently on insulin. Maximal oral therapy is defined as using at least two oral hypoglycaemic agents (OHAs) (metformin, sulphonylurea, TZDs, DPP-4 inhibitor) at maximal tolerated doses. Congruent with the pragmatic, translational nature of this trial, patients are also eligible if their responsible medical practitioner is of the opinion that insulin is appropriate despite the patient being on less than two OHAs or not at maximal dose. Patients are ineligible if they are >80 years old, have unstable cardiovascular disease, are unable to give informed consent or have a complex debilitating medical condition, *e.g.*, severe mental illness, end-stage cancer.

### Participant identification and recruitment

Patient identification is conducted by practices employing a number of methods to generate a comprehensive list of potentially eligible patients. Search methods vary by practice but include searching the practice electronic medical records database, using the Pen clinical audit tool [30], or obtaining a list of HbA1c results from the local pathology providers. Our previous research and pilot suggests an average general practice (of two full-time GPs) has 80 to 100 identified patients with T2D, 10% to 15% (8 to 15) of whom meet inclusion criteria.

Recruitment involves a letter from the practice inviting eligible patients to participate and a follow-up call from the PN and/or GP. The invitation letter states that participants may benefit from assessment and more intensive treatment of their diabetes and that insulin may be a part of that program. Patients are invited to express interest in receiving further details about the study, to attend the practice to learn more about the study from a member of the study team. If the patient agrees to participate, consent and baseline data are collected at that visit. Patients are asked to have their HbA1c checked and are subsequently excluded if the result is <7.5%.

### Study intervention

Our intervention is targeted at the decision to initiate insulin and the care processes involved in implementing that decision. The Stepping Up Program intervention (Additional file 2) is designed to address barriers we have identified. GPs and PNs in intervention practices participate in the Stepping Up Program elements: in-practice briefing and training visit, and ongoing support for practice and PN in working with patients.

The aim of the training is to ensure GP/PN teams have the knowledge and confidence to initiate a discussion with eligible patients about commencing insulin, knowing that they will be able to act on this within current routine clinical care using a simple, safe, convenient evidence-based algorithm. Referral or consultation with an Endocrinologist, CDE-RN or any other appropriate health professional will naturally be management options for GPs managing study patients. GPs and PNs are provided with patient packs for each of the participating patients whom they review.

In control group practices, GPs are sent a copy of Royal Australian College of General Practitioners (RACGP) guidelines for the management of T2D and a list of participating patients and asked to undertake a clinical review of those patients. Control group practices will be offered the Stepping Up training after the 12-month follow up.

Following recruitment and baseline data collection, participants are invited to attend their GP for an assessment to discuss their diabetes. For the first participant this is at a time when the Study CDE-RN is available to support the PN. Participants in intervention practices are managed according to the Stepping Up Program by GP and PN who have attended the Stepping Up Training. When participants attend, the GP reviews their diabetes and if appropriate makes a clear recommendation for the need to commence insulin, refers the participant to the PN and writes a prescription for Glargine Insulin. The participant sees the PN (supported by the Study CDE-RN) on that day for an insulin initiation assessment, during which time the PN and the Study CDE-RN work through the patient pack with the participant. At that visit the PN, supported by the CDE-RN, gives the first dose of Glargine insulin 10 units. The PN has the option to review the participant on day two, and observe the participant give their second dose of Glargine 10 units to themselves if they are not already comfortable to do this at home. Subsequently participants are asked to call the PN for review by phone every three days. The participant records fasting morning blood glucose in the record book provided and is encouraged to discuss the results with the PN and follow the simple protocol (see Additional file 3). After four weeks, if fasting blood glucose levels (FBGLs) are at target (<7), participants are reviewed by the GP and a three-day blood glucose level (BGL) profile is completed to identify the meal with the largest postprandial (PP) excursion. Apidra is then commenced at this meal and again adjusted to a simple protocol based on an average PPBGL over three days related to that mealtime (see Additional file 3). GPs review participating participants at least every four weeks. The GPs initiate and prescribe insulin, while the insulin adjustment is led primarily by PN and participant in discussion and in liaison with the GP as necessary.

All participants, even if not commencing insulin at the first GP/PN visit, continue to see the PN and GP with the aim of commencing insulin. GPs and PNs see participants on as many occasions as is clinically necessary over a period of up to 12 months drawing as needed on the Stepping Up Program manual and resources.

Participants in control practices are managed by their GP according to usual care (*e.g.*, referral, investigation, and adjustment of medication as the GP believes clinically appropriate).

### Specific role of the practice nurse

PNs lead and drive the dialogue with participants around the issue of intensifying treatment through insulin initiation. PNs do not prescribe or manage dosing of insulin without liaison with the GP. Our training directly addresses any GP or PN reluctance to initiate insulin, as well as developing in-practice systems to support the initiation process. This process is well within the legal scope of practice for PNs. Any clinical concerns beyond the conservative simple clinical protocol can be addressed through consultation with an endocrinologist or local CDE-RN in the usual manner. Ongoing care of complex and co-morbid conditions continues as per usual care.

### Data collection and outcomes measures

#### Outcomes

The primary outcome is change in HbA1c (measured as a continuous variable). Secondary outcome measures include the number of participants who successfully transfer to insulin and the proportion of participants who achieve HbA1c measurement of <7.0%. We will also collect data on other outcome measures of interest including the proportion of participants who achieve individualized HbA1c targets according to Australian Diabetes Society guidelines, changes in psychometric scores including AQoL-8D, PHQ-9 and PAID and net healthcare utilization and costs. Research assistant (RA) staff will collect participant data at baseline and at 12 months using the instruments and measures outlined in Table 1. HbA1c is also collected at six months.

**Table 1 T1:** Outcome measures and collection time points

**Measure**	**Baseline**	**6 months**	**12 months**
**Demographic and clinical measures:**			
Demographic data, duration of diabetes	X		
Biometric measures: weight, BMI, waist circumference	X		X
HbA1c	X	X	X
Lipids, U&E, spot urine albumin to creatinine ratio	X		X
Medication details, co-morbidities	X		X
**Psychological measures:**	X		X
Health status: AQoL-8D [31]	X		X
Depressive symptoms: PHQ-9 [32]	X		X
Diabetes-related distress: PAID [33]	X		X
Medication taking behaviours: MARS [34]	X		X
Beliefs about insulin: ITAS [35], additional single items taken from [36]	X		X
Patient experience: excerpts from GPAQ [37], Consumers Perception of Informational Continuity [38]	X		X

All participants (intervention and control) are provided with a BGL meter (Performa Nano™; Roche Diagnostics) and are instructed how to use the meter. Data from BGL meter are uploaded at each practice visit and at 12 months by PNs to a secure server.

A pre-printed pathology form (HbA1c) with participant and practice details entered is mailed out to study participants by the study RA five months after the baseline visit with the GP at which anthropometric data was collected. HbA1c results five to seven months from the baseline date will be accepted as the mid-study HbA1c.

Additional data will be collected to inform the economic evaluation: resources used to administer the intervention; subsequent changes in participant’s health service utilization during the 12-month follow-up period; and use and cost of medical services (data gathered by accessing health service and pharmaceutical data from Medicare Australia).

A practice characteristics survey is also collected at baseline. In addition, participating GPs and PNs complete a questionnaire that includes demographics, current perceptions and practices regarding insulin initiation, questions relating to insulin initiation and perceived participant willingness from the Diabetes Attitudes, Wishes, and Needs (DAWN) study [39], relational coordination [40], collaborative practice scale [41] and questions based on normalization process theory [42], and the interactional determinants of collaboration [43].

### Analysis

#### Power calculation and sample size

Our sample size calculation is based on the primary outcome. A total of 224 participants (average of three participants per practice) from 74 general practices are required to detect an absolute 0.5% mean HbA1c difference over 12 months between control and intervention groups with 80% power and a standard deviation (SD) of 1 using two-sided alpha of 0.05. Sample size calculation allows for a design effect of 1.05 and is based on a conservative estimate of the intra-cluster correlation (ICC) for HbA1c of 0.05 [44] and attrition rate of 10% for practices and participants.

In a community observational study [23], over a five-year period, about 2% of the community sample changed from oral treatment to insulin per year. We conservatively assume a background rate 10 times this or 20% per year in the control group. Based on our pilot study [29], we estimate 60% will start insulin in the intervention group. A total of 224 participants from 74 general practices will provide sufficient power to detect a 40% change in the proportion that transition to insulin (power = 99.9%, assuming an intra-cluster correlation of 0.3). We will measure and compare the proportion of participants in each group that reach HbA1c target although our sample size is not powered to detect a significant difference in that.

The study will also have at least 80% power to detect an effect size of 0.5 of 1 SD for psychosocial scores, assuming an ICC of 0.05.

We do not anticipate a significant confounding of the results by the attention received by control group participants. In control group practices, GPs will be advised to undertake a clinical review of participating participants. In these practices, the PN will not receive training or support. In our intervention the PN once trained plays a critical enabling role in facilitating a simple in-practice system for insulin initiation. Without access to a trained PN and this system, background rates of insulin initiation by GPs in the control arm are likely to approximate those quoted above.

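### The primary sample-size paragraph does not reproduce from its own inputs: the design effect is 1.10 rather than 1.05, and 224 participants give about 89–93% power rather than 80%

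*Protocol article*

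**What the plan says.** All the figures are in the protocol article, Analysis, under Power calculation and sample size.

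- Size and target difference: "A total of 224 participants (average of three participants per practice) from 74 general practices are required to detect an absolute 0.5% mean HbA1c difference".
- Error rates and variability: "with 80% power and a standard deviation (SD) of 1 using two-sided alpha of 0.05".
- Clustering: "Sample size calculation allows for a design effect of 1.05 and is based on a conservative estimate of the intra-cluster correlation (ICC) for HbA1c"; the ICC value given is 0.05.
- Losses: "attrition rate of 10% for practices and participants".

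The next paragraph of that section uses a different ICC, 0.3, for the secondary outcome of transition to insulin. The article gives no allocation ratio.

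**The concern.** The paragraph supplies everything needed to check it, and two of its figures fail the check. The design effect does not match the cluster size and ICC given beside it. The participant total is also well above what the stated difference, SD, alpha and power require, even after the stated allowances for clustering and attrition.

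This paragraph justifies the size of a cluster trial on its primary outcome, and the Statistical analysis section commits to CONSORT reporting for cluster trials. As written, the trial would report a power and a design effect that its design does not have. Recruitment was still under way according to Trial status, so anyone judging a shortfall would also start from these figures.

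**Working it through.** **Inputs.** From Power calculation and sample size: difference 0.5, SD 1, two-sided alpha 0.05, power 80%, 224 participants, 74 practices, three per practice, ICC 0.05, design effect (DE) 1.05, attrition 10% for practices and participants. Assumption: 1:1 allocation. The attrition wording allows two readings: 10% once (retention 0.90), or 10% at each level (retention 0.9 × 0.9 = 0.81). Both are carried through.

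**Step 1: design effect.** DE = 1 + (m − 1) × ICC.

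- m = 3: 1 + 2 × 0.05 = 1.10. Using 224/74 = 3.03 gives 1.101.
- m = 2.7, that is, three less 10%: 1 + 1.7 × 0.05 = 1.085.
- To obtain 1.05 one needs m = 2 at ICC 0.05, or ICC = 0.05/2 = 0.025 at m = 3. Neither is stated.

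**Step 2: attempt to reproduce 224 at 80% power.** n per arm = 2 × (1.960 + 0.842)² × 1² / 0.5² = 62.8, so 63 (64 by the t-test). The total is 126–128 before inflation. Then N = total × DE / retention:

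| DE | Before attrition | 10% once (÷ 0.90) | 10% at both levels (÷ 0.81) |
|---|---|---|---|
| 1.05 (stated) | 133–135 | 147–150 | 164–166 |
| 1.10 (from m = 3) | 139–141 | 154–157 | 172–174 |

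None of these is 224. Other conventions (no attrition, division by 0.8, multiplication by 1.1 or 1.21) do not come within 3% of it at 80% power either.

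**Step 3: power that 224 gives.** Effective n per arm = 224 × retention / DE / 2.

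| DE | Retention | Effective n per arm | Power |
|---|---|---|---|
| 1.05 | 0.90 | 96.0 | 93% |
| 1.05 | 0.81 | 86.4 | 90–91% |
| 1.10 | 0.90 | 91.6 | 92% |
| 1.10 | 0.81 | 82.5 | 89% |

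With DE 1.10 and retention 0.81, the difference detectable with 80% power is about 0.44%.

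**Step 4: sensitivity.** A cluster-level t-test on 66 practices of 2.7 gives 88%. For unequal practice sizes, DE = 1 + ((CV² + 1) × 3 − 1) × 0.05. The document gives no CV, so these values are assumptions: CV 0.5 gives DE 1.1375 and power of 88% (retention 0.81) or 91% (0.90); CV 1.0 gives DE 1.25 and power of 85% or 89%.

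**Step 5: where 224 might come from.**

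- 90% power, DE 1.05, attrition at both levels: 170 × 1.05 / 0.81 = 220.4, so 221; with t-test numbers, 172 × 1.05 / 0.81 = 223.0. With DE 1.10 the same route gives 231–234.
- 80% power, ICC 0.3, attrition once: DE = 1 + 2 × 0.3 = 1.6, and 126 × 1.6 / 0.9 = 224 exactly. The ICC of 0.3 is the one the article quotes for insulin transition.
- A larger SD: 224 gives 80% power at an SD between about 1.14 (DE 1.10, retention 0.81) and 1.24 (DE 1.05, retention 0.90).
- For the practice count only: two analysed per practice gives DE 1.05, and 126 × 1.05 / 0.9 / 2 = 73.5, so 74 practices. This conflicts with three per practice less 10%.

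**The case against.** The strongest reply is that the trial is larger than its stated assumptions need, so nobody is harmed. Much of this stands. Every power computed at SD 1 from the stated inputs is above 80%, even with very uneven practice sizes. Correcting the design effect alone costs about one percentage point of power. The planned analysis allows for clustering whatever value was used in planning, so the estimate, its standard error and the test are unaffected.

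A second reply is that 80% was meant as a floor, as it is for the psychosocial scores in the same section. The primary sentence does not say that: it presents 224 and 74 as the numbers required. Rounding up does not explain the gap either, since 224 exceeds the computed requirement by 50 (against 174) to 77 (against 147).

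Three stronger readings are tempting, and the document supports none of them.

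- *The trial was really sized at 90% power and 80% is a slip.* That route fits, but so does 80% power with ICC 0.3, and the first route relies on the very design effect that is in error.
- *The understated design effect leaves the trial underpowered.* On the stated inputs it does not. That would need a larger SD or ICC than the paragraph gives.
- *About 174 participants in 58 practices would be enough, so the target can be lowered.* That rests on one reading of the attrition rule, on equal practice sizes, and on the stated SD and ICC being the ones actually used, which is the point in doubt.

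**Conclusion.** The point holds as an internal inconsistency in the primary sample-size statement. The design effect should be 1.10 (1.085 if cluster size is taken after attrition), not 1.05. The stated 80% power does not correspond to 224 participants: the requirement is about 147–166 with DE 1.05 or 154–174 with DE 1.10, and 224 gives about 89–93% power, somewhat less with unequal practice sizes.

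This rests on 1:1 allocation and on the two readings of the attrition rule. The failure to reproduce is certain under either reading; its cause is not. Power, SD, ICC, cluster size or the attrition rule could each be the misreported item. If the stated inputs are the true ones, the error is in the safe direction.

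**What to change.** Correct the design effect to 1.10 and restate the power so that the paragraph can be recomputed. If the stated inputs are confirmed and attrition applies at both levels, suitable wording would be:

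> With three participants per practice, ICC 0.05 (design effect 1.10), SD 1 and 10% loss of practices and of participants, 224 participants from 74 practices give about 89% power to detect a difference of 0.5% (80% power to detect 0.44%).

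If the 10% loss was applied once, the power figure becomes about 92%, and the loss should be worded accordingly. If the trial was sized on another ICC, SD, cluster size, attrition rule or power, the sponsor should state those inputs instead, so that 224 and 74 follow from them. The allocation ratio should be given in the same sentence.

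The cost is wording only. The recruitment target of 224 participants from 74 practices stays as it is.
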